## Interim analysis and stopping criteria

- - 1. All ROSC (Return of Spontaneous Circulation) Events

If the number of ROSC events in one group significantly exceeds that of the other group, as determined by a chi-square test in a 2x2 table, and if this difference reaches statistical significance (p-value < 0.05), the study may be terminated.

- - 1. Adverse Events

The known potential adverse event related to the ventilator that could be assessed in this study is barotrauma (pressure-related injury to the airway). However, considering that the study subjects are OHCA (out-of-hospital cardiac arrest) patients, and not all of them can be evaluated for the occurrence of barotrauma under standard medical practice, the threshold for adverse events in this study is set at 5%. If more than 15 cases of potential barotrauma (e.g., pneumothorax) occur in the experimental group, the study must be terminated.

- - 1. Other criteria
       1. Changes in government emergency medical services policies
       2. The APV is found to be harmful to humans during the study
       3. Major compromise to the EMS work due to the study

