## Outcome measurement

- - 1. Primary outcome

The primary outcome of the trial is any ROSC (defined as prehospital ROSC or ROSC achieved after in-hospital resuscitation).

- - 1. Secondary outcomes

The secondary outcomes include the following:

- Prehospital ROSC: ROSC before hospital arrival
- 24-hour survival
- Survival to discharge
- Neurological function on discharge
- Ventilation rate in prehospital resuscitation
- Tidal volume in prehospital resuscitation
- End-tidal CO2 level in prehospital resuscitation
- Chest compression fraction in prehospital resuscitation
- Intravenous catheter insertion in prehospital resuscitation
- Epinephrine injection in prehospital resuscitation
- Satisfaction of EMT in prehospital resuscitation (Appendix 2)

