# Data and Safety Monitoring Boards and Interim Analysis

This study has established a Data and Safety Monitoring Board (DSMB) in accordance with the standards of the National Institutes of Health (NIH). The DSMB will review the completeness of the data and monitor for any obvious abnormalities that could compromise the patients' safety every six months. Additionally, when enrollment reaches half of the target sample size (130 participants), the board will independently conduct an interim analysis. If any concerning situations arise, the board will consult with the principal investigator to determine whether the study should be suspended. The DSMB meetings will be held every six months.

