# Analytic Plan

Statistical Package for the Social Sciences (version 26.0; IBM Corp., Armonk, NY, USA) will be used for the statistical analyses in this study. Intention to treat analysis will be adopted for comparing outcomes between interventions. Firstly, descriptive statistics of demographics (Table 1), ventilation parameters (Table 2), and outcomes (Table 3) among APV group and BVM group will be presented as number (percentage) for categorical variables and median (interquartile range) for continuous variables. Categorical variables will be compared using Pearson’s chi-square test or Fisher’s exact test, while continuous variables will be compared using Mann–Whitney U test. Secondly, multivariable logistic regression will be conducted to investigate the association of different ventilation interventions and patients’ outcomes, adjusting for potential confounders. Subgroup analysis, presented as a forest plot, will also be performed to investigate the impact of different interventions on outcomes in different subgroups. We will also compare the adjusted absolute difference between ventilation parameters measured in the APV and BVM group using the linear mixed-effects model (LMM). For the LMM, variables including demographics, prehospital information, resuscitation managements were included as fixed effects, whereas each patient will be modeled as a random effect. Two tail p-values <0.05 will be considered as statistically significant and will be corrected with Bonferroni correction in post-hoc analyses.

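### The interim rule allows stopping on ROSC at an unadjusted p<0.05 and the final test reuses p<0.05; acted on as written, one interim gives about 8.3% to 9.1% type I error, not 5%

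*Protocol*

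**What the plan says.** The Protocol section on outcome measurement states: "The primary outcome of the trial is any ROSC". The section on interim analysis and stopping criteria makes the same endpoint its only efficacy criterion. It is worded in both directions, "If the number of ROSC events in one group significantly exceeds that of the other group", and assessed "as determined by a chi-square test in a 2x2 table"; then "if this difference reaches statistical significance (p-value < 0.05), the study may be terminated".

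The Analytic Plan sets the final level: "Two tail p-values <0.05 will be considered as statistically significant". The only multiplicity adjustment is that p-values "will be corrected with Bonferroni correction in post-hoc analyses". No alpha spending, group-sequential boundary or reduced final level is stated. The sample size section also uses a two-tailed alpha of 0.05.

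On timing, the section on the monitoring board places one interim "when enrollment reaches half of the target sample size (130 participants", at which "the board will independently conduct an interim analysis". The sample size section gives 260 as the superseded target and 514 as the current one. The Timeline has an interim analysis row in both the 2024 and the 2025 plan.

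**The concern.** Two tests of one hypothesis, each at the full 5% level and either able to yield a positive result, have a combined false-positive probability above 5%. The protocol fixes the endpoint, the interim test and both thresholds, and nothing in it compensates for the extra look.

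Two things are at stake. A significant ROSC result could not be reported as controlled at 5%. A stop at 130 patients would also tend to exaggerate the benefit, because only large observed differences cross the threshold at that size. It would leave about a quarter of the planned patients for survival and neurological function.

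**Working it through.** **Inputs from the Protocol.** ROSC 56.7% vs 43.3%, two-sided alpha 0.05, power 0.80, 1:1 allocation, design effect 1.12, dropout 5%, final size 514 (Sample Size Estimation); interim at 130 (monitoring board section); p<0.05 at the interim and at the end.

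**The plan's own figure.** With pooled variance under the null,

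n per arm = [1.960·√(2·0.5·0.5) + 0.842·√(0.567·0.433 + 0.433·0.567)]² / 0.134² = (1.386 + 0.590)² / 0.01796 ≈ 217.4, so 218.

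Then 2 × 218 = 436; 436 × 1.12 = 488.3, taken as 488; 488 / 0.95 = 513.7, so 514. The plan's 514 is reproduced. It assumes one test at 5%.

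**Overall error.** Under the null, the interim and final statistics are approximately bivariate normal with correlation √t, where t is the fraction of patients at the interim. The overall error is 1 − P(|Z₁| < 1.96 and |Z₂| < 1.96).

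| Efficacy looks, each at p<0.05 | t | Overall two-sided error | In favour of APV |
| --- | --- | --- | --- |
| One interim at half (130/260 or 257/514), plus final | 0.50 | 8.3% | 4.2% |
| One interim at 130 of 514, plus final | 130/514 = 0.253 | 9.1% | 4.5% |
| Interims at 130 and 257 of 514, plus final (second look and its timing assumed) | 0.253, 0.50 | 11.3% | 5.7% |

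The nominal values are 5% and 2.5%. The two-look rows come from the bivariate normal integral and the three-look row from simulation. A binomial simulation of the chi-square test with one interim, at ROSC rates of 30% to 50%, gives 8.2% to 9.3%.

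**Exaggeration after an early stop.** With 65 patients per arm and true rates of 56.7% and 43.3%, just over 31% of trials would cross p<0.05 in favour of APV. The smallest difference that crosses is about 17 points (11/65). Trials that cross report 23.2 points on average, against a true 13.4.

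**Candidate boundaries.**

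| Boundary (interim / final p) | Interim at 257 | Interim at 130 | Both |
| --- | --- | --- | --- |
| Haybittle-Peto, 0.001 / 0.05 | 5.02% | 5.06% | 5.08% |
| O'Brien-Fleming values for a look at half, 0.0052 / 0.048 | 5.0% | 5.2% | not computed |

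At 130 of 514 the O'Brien-Fleming interim level is about 0.0001, with a final level of about 0.04996.

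**The case against.** **Stopping is discretionary.** The rule permits termination and does not require it, and the board is to consult the principal investigator. If the board never stopped on this criterion, the error would return to 5%. This stands as a qualification: the percentages describe the rule acted on whenever it is met. Discretion without a boundary does not restore 5%, though; it leaves the error unknown.

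**It may be meant as a safety rule.** The figures count crossings in both directions, and only about half favour APV. But the wording covers either group exceeding the other, so it includes stopping for benefit. Barotrauma and harm have their own criteria in the same section.

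**It belongs in the statistical analysis plan.** This would hold if the protocol had left the boundary open. It names the test and both thresholds, so an analysis plan with a proper boundary would contradict it.

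**Stronger readings.** A reader might infer from the two timeline rows that two interims are planned and quote 11% outright. The documents do not support that. The text describes one interim, and the month cells are blank as read, so the rows could equally show one analysis spanning or moved across the year end. Nor are the six-monthly board meetings efficacy looks: their stated purpose is data completeness and safety.

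A reader might also add the effect of a chi-square that ignores clustering, giving 10.5% to 11.5% with one interim if the design effect of 1.12 is ignored at both looks. That is a separate problem, since it would raise even a single final test to 6.4%. It does not belong in the size of this one.

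**Conclusion.** The point holds. As written, the interim and final rules together do not keep the 5% level on which the trial was sized. With the one interim that the text describes, the overall two-sided error is 8.3% to 9.1%, depending on whether the look falls at half the patients or at 130 of 514. This assumes that every crossing leads to a stop and a claim, and that the final test is otherwise valid at 5%. The 11.3% figure is conditional on a second efficacy look and on its assumed placement at 257. The exaggeration to about 23 points applies only to trials that cross at 130 in favour of APV, under the protocol's assumed rates.

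This should be corrected because it bears directly on the primary conclusion and the remedy is cheap.

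**What to change.** 1. Reconcile the interim timing: 130 is half of the superseded 260, while half of 514 is 257.
2. State how many efficacy looks there will be and when, and bring the Timeline rows into line.
3. Replace p<0.05 in the stopping criteria with a conservative boundary. Haybittle-Peto (interim p<0.001, final p<0.05) works at either timing or at both. If O'Brien-Fleming is preferred, compute it for the actual information fraction; about 0.005 and 0.048 apply only to a look at half.
4. Use a test that accounts for the clusters at the interim.
5. If an interim at p<0.05 has already been done, account for that look in the final level. The documents do not say whether it has.

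The cost is a short protocol amendment and matching wording for the monitoring board. Early stopping for ROSC becomes harder. Loss of final power is negligible: with Haybittle-Peto the final level stays at 0.05, or about 0.0494 to 0.0498 if exactly 5% overall is wanted with one interim. If a look at p<0.05 has already been taken, a wording change alone will not repair the error rate and the final level must carry the adjustment.

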| 11 | T Tangpaisarn, 2023  [18] | The effects of mechanical versus bag-valve ventilation on gas exchange during cardiopulmonary resuscitation in emergency department patients: A randomized controlled trial (CPR-VENT) | In cardiac arrest patients in ED, the RCT compared ABG parameter, patient outcome and pneumothorax between  MV( peak pressure 60 cm-H_2_O) and BVM. | The ABG parameter, patient outcome and pneumothorax showed no differences between 2 groups. |
| 12 | J Shin, 2024  [19] | Automatic Mechanical Ventilation vs Manual Bag Ventilation During CPR: A Pilot Randomized Controlled Trial | A pilot RCT comparing ABG parameter, ventilation and patient outcome in OHCA patients between  MV( peak pressure 70 cm-H_2_O) and BVM. | MV had lower tidal volume (267 vs. 507mL, p<0.001) and lower minute ventilation (3.1 vs. 6.7L p=0.009),  but no difference between outcomes.  No ABG parameters difference between groups. |

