# Sample Size Estimation

In the original version of sample size calculation, we chose a secondary outcome (ventilation rate) to be the reference to calculate the sample size. Because we couldn’t find any studies with a similar trial design and primary outcome as our study. The original sample size was 260 patients. However, in August 2024, we identified some comparable studies to guide our calculations more precisely.

We chose the pilot study by Shin et al., which compared automatic mechanical ventilation (MV) with manual bag ventilation (BV) during CPR [19]. In that study, the primary outcome, any ROSC, was achieved in 56.7% of the MV group and 43.3% of the BV group—values closely aligning with our expected ROSC rates. Thus, we conducted an initial power analysis in G*Power 3.1 using the following parameters: Z test family, difference between two independent proportions, two-tailed test, proportions of 0.567 and 0.433, alpha of 0.05, power of 0.8, and equal allocation (1:1). This analysis suggested 218 patients per arm, totaling 436.

To account for the clustering effect due to randomization at the EMS team level, we included an intraclass correlation coefficient (ICC). Our EMS teams are expected to recruit 3 patients per cluster (over 14 days). Given the substantial variability in OHCA patient conditions, we assumed a low ICC of 0.06. The design effect was therefore calculated as 1+(3−1) ×0.06=1.12, adjusting our sample size to 488. Finally, with an estimated 5% dropout rate, the final required sample size was increased to 514 patients.

Figure 3. Sample size calculation by G*Power 3.1

[figure not shown]

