# Data Collection and Follow-up

Data will be collected in the REDCap database set up at National Taiwan University Hospital. The following variables will be gathered from the rescue reporting form: patient demographics (age and sex), pre-existing comorbidities (hypertension, diabetes mellitus, COPD, asthma, liver disease, kidney disease, heart disease, seizure, psychotic disorder, and cancer), arrest characteristics (witnessed arrest and bystander CPR), arrest location (household, workplace, public space, and nursing home), and EMT-performed procedures (oral/nasal airway, SGA, ETT, mechanical CPR, AED, defibrillation, IO/IV catheter, epinephrine injection, and normal saline infusion). Prehospital ROSC will also be reported on the form. These data will be collected on a weekly basis.

Other prognostic outcomes (any ROSC, 24-hour survival, survival to discharge, and neurological function at discharge) will be collected from the reports of the hospitals to which the patients are sent. Follow-up frequency for these outcomes will be one month.

Ventilation and chest compression feedback data will be exported from the Zoll X-series in .csv format. These files will be uploaded to the REDCap database on a weekly basis.

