# Dummy Tables

| Table 1. Baseline characteristics | | |
| --- | --- | --- |
|  | APV | BVM |
|  | (n=XXX) | (n=XXX) |
| Age, years (mean ± SD) | XX ± XX | XX ± XX |
| Males, n (%) | XX (XX.X%) | XX (XX.X%) |
| Pre-existing comorbidity |  |  |
| Diabetic mellitus, n (%) | XX (XX.X%) | XX (XX.X%) |
| Hypertension, n (%) | XX (XX.X%) | XX (XX.X%) |
| Cancer, n (%) | XX (XX.X%) | XX (XX.X%) |
| COPD, n (%) | XX (XX.X%) | XX (XX.X%) |
| Asthma, n (%) | XX (XX.X%) | XX (XX.X%) |
| Stroke, n (%) | XX (XX.X%) | XX (XX.X%) |
| Liver disease, n (%) | XX (XX.X%) | XX (XX.X%) |
| Kidney disease, n (%) | XX (XX.X%) | XX (XX.X%) |
| Heart disease, n (%) | XX (XX.X%) | XX (XX.X%) |
| Seizure, n (%) | XX (XX.X%) | XX (XX.X%) |
| Psychotic disorder, n (%) | XX (XX.X%) | XX (XX.X%) |
| Witnessed arrest, n (%) | XX (XX.X%) | XX (XX.X%) |
| Bystander CPR, n (%) | XX (XX.X%) | XX (XX.X%) |
| Arrest location |  |  |
| Household, n (%) | XX (XX.X%) | XX (XX.X%) |
| Working place, n (%) | XX (XX.X%) | XX (XX.X%) |
| Public space, n (%) | XX (XX.X%) | XX (XX.X%) |
| Nursing home, n (%) | XX (XX.X%) | XX (XX.X%) |
| Others, n (%) | XX (XX.X%) | XX (XX.X%) |
| Oral airway, n (%) | XX (XX.X%) | XX (XX.X%) |
| Nasal airway, n (%) | XX (XX.X%) | XX (XX.X%) |
| SGA, n (%) | XX (XX.X%) | XX (XX.X%) |
| ETT, n (%) | XX (XX.X%) | XX (XX.X%) |
| Mechanical CPR, n (%) | XX (XX.X%) | XX (XX.X%) |
| AED, n (%) | XX (XX.X%) | XX (XX.X%) |
| Defibrillation, n (%) | XX (XX.X%) | XX (XX.X%) |
| IO, n (%) | XX (XX.X%) | XX (XX.X%) |
| IV, n (%) | XX (XX.X%) | XX (XX.X%) |
| Epinephrine, n (%) | XX (XX.X%) | XX (XX.X%) |
| Normal saline, n (%) | XX (XX.X%) | XX (XX.X%) |

| Table 2. Ventilation parameters between patients in APV and BVM group | | |
| --- | --- | --- |
|  | APV | BVM |
|  | (n=XXX) | (n=XXX) |
| Ventilation rate, bpm (median ± IQR) | XX ± XX | XX ± XX |
| Tidal volume, mL (median ± IQR) | XX ± XX | XX ± XX |
| EtCO2, mmHg (median ± IQR) | XX ± XX | XX ± XX |

| Table 3. Outcome comparison between patients in APV and BVM group | | |
| --- | --- | --- |
|  | APV | BVM |
|  | (n=XXX) | (n=XXX) |
| Prehospital ROSC, n (%) | XX (XX.X%) | XX (XX.X%) |
| Any ROSC, n (%) | XX (XX.X%) | XX (XX.X%) |
| 24-hour survival, n (%) | XX (XX.X%) | XX (XX.X%) |
| Survival to hospital discharge, n (%) | XX (XX.X%) | XX (XX.X%) |
| Good neurological function after discharge, n (%) | XX (XX.X%) | XX (XX.X%) |

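### The barotrauma stopping rule pairs a 5% threshold with a count of more than 15 cases, which match at no planned sample size, and the count cannot enforce 5% before late in enrolment

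*Protocol*

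**What the plan says.** Under Interim analysis and stopping criteria, the Protocol names barotrauma as the known ventilator-related harm and notes that not every patient can be evaluated for it. It then states that "the threshold for adverse events in this study is set at 5%. If more than 15 cases of potential barotrauma" occur in the experimental group, termination is mandatory. The denominator of the 5% is not given.

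The sizes against which the pairing can be checked are these:

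- Sample Size Estimation: "The original sample size was 260 patients", and after the August 2024 recalculation "the final required sample size was increased to 514 patients".
- Data and Safety Monitoring Boards and Interim Analysis: "when enrollment reaches half of the target sample size (130 participants), the board will independently conduct an interim analysis".

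On data sources, Data Collection and Follow-up says: "Other prognostic outcomes (any ROSC, 24-hour survival, survival to discharge, and neurological function at discharge) will be collected from the reports of the hospitals". Barotrauma is not in that list. It is also not among the outcomes under Outcome measurement or in the Dummy Tables.

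**The concern.** Two thresholds stand in consecutive sentences, a rate and a count, and nothing says how one yields the other. If the count is meant to express the rate, it should equal about 5% of some planned number of patients. If the two are separate, the Protocol should say which governs. Suppose the DSMB saw 8 cases in 100 APV patients: the observed rate is 8%, above the stated 5%, yet the count is only half of what forces a stop.

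This matters because it is the only numeric rule in the Protocol that makes termination obligatory (the ROSC rule is permissive). It covers the harm that the Backgrounds section calls a key concern, in a trial run under a waiver of consent. A fixed total is also hard to reach early, which is when stopping would spare most patients.

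**Working it through.** **1. The planned size.** Inputs from Sample Size Estimation: 218 per arm, design effect 1.12, dropout 5%.

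- 218 × 2 = 436
- 436 × 1.12 = 488.3, taken as 488
- 488 / 0.95 = 513.7, rounded up to 514, so 257 per arm

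The Protocol's 514 is reproduced.

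**2. Where the two thresholds agree.** The smallest count exceeding 5% of n is floor(0.05n) + 1. Setting this equal to 16 gives n = 300 to 319. If 5% means at least 5%, the range is 301 to 320.

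| Size | Origin | 5% of it | First count above 5% | 16 cases as a rate |
|---|---|---|---|---|
| 65 | half of the 130-participant interim | 3.25 | 4 | 24.6% |
| 130 | original arm (260/2) | 6.5 | 7 | 12.3% |
| 218 | unadjusted arm | 10.9 | 11 | 7.3% |
| 244 | arm before dropout (488/2) | 12.2 | 13 | 6.6% |
| 257 | current arm (514/2) | 12.85 | 13 | 6.2% |
| 260 | original total | 13.0 | 14 | 6.2% |
| 436 | unadjusted total | 21.8 | 22 | 3.7% |
| 488 | total before dropout | 24.4 | 25 | 3.3% |
| 514 | current total | 25.7 | 26 | 3.1% |

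No size falls in 300 to 319 or in 301 to 320. An evaluable-only denominator would be smaller than the arm, and so further from 300.

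**3. When the count fires.** P(X ≥ 16) for X binomial(n, p). The Protocol gives no expected barotrauma rate, so the true rates below are assumptions, shown as a range.

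| True rate | n = 128 (half of the current arm) | n = 257 (full arm) |
|---|---|---|
| 5% | 0.0007 | 0.218 |
| 8% | 0.05 | 0.88 |
| 10% | 0.21 | 0.99 |
| 15% | 0.82 | 1.00 |

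At 10%, the expected number of APV patients needed to reach 16 cases is 16/0.10 = 160.

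**4. A proportional boundary.** Take the smallest k with P(X ≥ k | n, 0.05) ≤ 0.05. For n = 128, k = 12 has tail 0.027 and k = 11 has tail 0.057, so the boundary is 12. The chance of having stopped by 128 becomes:

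| True rate | Count alone | With 12 of 128 |
|---|---|---|
| 8% | 0.05 | 0.33 |
| 10% | 0.21 | 0.64 |
| 15% | 0.82 | 0.98 |

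**5. Cost in false stops.** An exact patient-by-patient recursion to n = 257 at a true 5% gives an overall stopping probability of 0.218 with the maximum alone and 0.220 with 12 of 128 added. At a true 10%, both give 0.988.

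**6. Why not stop at a bare observed 5%.** P(X ≥ 13 | 257, 0.05) = 0.52. That rule would end the trial about half the time when the true rate is exactly at the threshold.

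**The case against.** The binding instruction is clear by itself. A DSMB can count to 16 without a denominator, and the 5% can be read as the rationale for the count and not as a second trigger. At 257 per arm the count behaves reasonably. Any fixed total is slow early, and at a true 10% it still stops the trial with probability 0.99. The six-monthly DSMB review and the separate criterion that the APV is found harmful both allow an earlier stop.

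Much of this stands: the rule can be operated, and the gap at full enrolment is small. But if the 5% is the rationale, it does not produce 15 at any planned size. The discretionary routes neither say which figure governs nor set a level for acting.

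Three stronger readings are tempting and not supported.

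- A reader might infer that the rule gives no protection. It does, mainly in the second half of enrolment.
- A reader might judge it at the 130-participant interim, where about 65 APV patients give a firing probability of 0.0005 at an assumed 10%. The rule is not tied to that look; it applies whenever the 16th case occurs.
- A reader might infer that barotrauma will not be recorded. The Protocol only omits it from its lists. The rescue form, case report forms and any DSMB charter are not shown and may cover it.

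**Conclusion.** The point holds as a wrong threshold in a binding safety rule, and it should be fixed. The mismatch between 5% and more than 15 cases is exact arithmetic and does not depend on which planned size is taken as the denominator. Its size at full enrolment is modest: the stop comes at 6.2% of 257, where the first count above 5% would be 13. The practical weakness is timing. At half of the current arm, a rate assumed to be double the threshold would have triggered the rule only about one time in five.

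The timing figures rest on assumed true rates of 8% to 15%, 1:1 allocation, independent events and all enrolled APV patients as the denominator. The missing data item is a secondary matter of detail.

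**What to change.** Amend the stopping paragraph as follows.

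- State the denominator: APV patients enrolled to date, with the number assessed for barotrauma reported alongside, since not all can be evaluated.
- Keep more than 15 cases as the overall maximum.
- Add a boundary at DSMB reviews: stop if the cases so far give an exact one-sided binomial P of at most 0.05 against a 5% rate. At half of the current arm this is 12 of 128. Other review sizes depend on accrual and should be computed from the number actually enrolled. By 206 APV patients the boundary (17) lies above 16, so the present maximum governs from about there. The DSMB may prefer a looser or stricter level.

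As a minor accompanying change, add two items to the hospital-report list in Data Collection and Follow-up, for both arms: assessed for barotrauma (yes/no), and pneumothorax or other barotrauma present (yes/no). The rule then has a named source. A trial in the Literature Review already made the two-arm comparison: "The ABG parameter, patient outcome and pneumothorax showed no differences between 2 groups".

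The cost is one amendment needing IRB approval, one or two fields on reports already obtained, and a look-back for patients already enrolled. With the single look at 128, the statistical cost is the rise from 0.218 to 0.220 in the chance of stopping at a true 5%; more looks would add somewhat to it.

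### The barotrauma stopping rule is a raw count in the APV arm alone, with no BVM comparison and no denominator of evaluated patients, so the count cannot show whether APV causes excess harm

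*Protocol*

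**What the plan says.** Under Interim analysis and stopping criteria, the Adverse Events item names barotrauma as the known potential harm of the ventilator that the study could assess. It notes that "not all of them can be evaluated for the occurrence of barotrauma under standard medical practice", gives a 5% threshold without saying of what, and then fixes the rule: "If more than 15 cases of potential barotrauma (e.g., pneumothorax) occur in the experimental group, the study must be terminated".

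Three neighbouring texts bear on it:

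- The ROSC rule in the same section compares the arms with a 2x2 chi-square test and permits a stop rather than requiring one.
- The section on the Data and Safety Monitoring Boards has the board review safety every six months and consult the principal investigator on suspension if something concerning arises.
- Data Collection and Follow-up takes any ROSC, survival and neurological function from hospital reports. Barotrauma is not among the variables listed there, under Outcome measurement or in the dummy tables.

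**The concern.** Every enrolled patient is ventilated through an advanced airway during resuscitation, in either arm. Some barotrauma may therefore occur under both methods. A count taken in one arm cannot separate injury due to the device from injury common to both.

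The paragraph also accepts that ascertainment is incomplete, yet the rule uses a raw number of cases. The same 10 detected cases mean one thing if 50 APV patients were evaluated and another if 250 were. So the rule can end the trial when the arms do not differ, and a count that stays under the limit gives reassurance of unknown strength. This is fixed in the protocol in mandatory terms, so a separate analysis plan could not repair it without contradicting it.

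**Working it through.** **Arm size.** Inputs from Sample Size Estimation: ROSC 56.7% and 43.3%, two-sided alpha 0.05, power 80%, 1:1 allocation.

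- The two-proportion formula without continuity correction gives 218 per arm, 436 in all, as the protocol states.
- Design effect: 1 + (3 − 1) × 0.06 = 1.12, and 436 × 1.12 = 488.3, stated as 488.
- Dropout: 488 / 0.95 = 513.7, so 514, or 257 per arm.

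The protocol's figures reproduce.

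**Equal harm.** More than 15 means 16 or more. Sixteen of 257 is 6.2%. With 16 cases in each arm the difference is zero and termination is still mandatory. No assumption about ROSC is needed.

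**Chance of meeting the rule by overall detected APV rate.** With X binomial(257, p), P(X ≥ 16) is 6% at p = 4%, 22% at 5%, 48% at 6% and 88% at 8%. The BVM rate does not enter.

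**If evaluation depends on ROSC.** Assumptions not in the documents: only patients with any ROSC are evaluable, and the risk q among them is the same in both arms. Evaluable patients are then 257 × 0.567 = 145.7 and 257 × 0.433 = 111.3, a ratio of 1.31. Cases are binomial(257, ROSC rate × q), ignoring clustering:

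| q | Expected cases at 56.7% / 43.3% ROSC | P(≥ 16) at 56.7% | P(≥ 16) at 43.3% |
|---|---|---|---|
| 5% | 7.3 / 5.6 | 0.3% | <0.1% |
| 6% | 8.7 / 6.7 | 1.6% | 0.1% |
| 8% | 11.7 / 8.9 | 13% | 2% |
| 10% | 14.6 / 11.1 | 39% | 9% |
| 12% | 17.5 / 13.4 | 68% | 26% |
| 15% | 21.9 / 16.7 | 93% | 61% |

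Holding the evaluable numbers fixed at 146 and 111 changes these by about one percentage point at most (69% and 94% in the last two rows of the APV column).

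**Sensitivity to the evaluability assumption.** If half of the non-ROSC patients are also evaluable, the evaluable shares are 0.567 + 0.5 × 0.433 = 0.7835 and 0.433 + 0.5 × 0.567 = 0.7165. The ratio of detected cases falls to 1.09. At q = 10% the chances become 86% and 75%. The effect of ROSC shrinks, but the rule is met more often in either case.

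**Timing.** At q = 10% with only ROSC patients evaluable, the chance of having reached 16 cases is 0.25% after 128 APV patients and 8% after 193. Most such stops would come in the last quarter of enrolment.

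**The case against.** An absolute cap on harm in the device arm can be a deliberate safety choice, and consent is waived for all participants, which makes a firm limit easier to defend. That stands: nothing in the documents shows that a cap as such is wrong, and this point does not ask for it to be replaced by a discretionary review.

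A reader might infer that the rule penalises APV for the ROSC benefit the trial hopes to show. The documents do not support this as a finding. They say only that some patients cannot be evaluated, not which ones. Patients without prehospital ROSC may still be resuscitated in hospital, because the primary outcome counts ROSC achieved there, so evaluation need not depend on ROSC. The documents also give no barotrauma risk. At 6% or less among evaluable patients, with only ROSC patients evaluable, the rule is met less than 2% of the time.

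Nor is the count the only safeguard. The DSMB reviews safety every six months, and a separate criterion covers the APV being found harmful. Harm below 16 cases could still stop the trial, so the claim that it would go unnoticed is too strong. What remains is that the board would have a count it could not interpret.

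The literature row on the emergency-department trial ("The ABG parameter, patient outcome and pneumothorax showed no differences between 2 groups") shows that a by-arm comparison has been made elsewhere. It does not show that this trial's rule is wrong.

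**Conclusion.** The point holds in a limited form. The text mandates termination on a single-arm count, with neither a comparator nor an evaluated denominator, while acknowledging incomplete evaluation. The 16-and-16 example follows from the text and the planned arm size alone. The probabilities are illustrations: they rest on assumed risks, on the any-ROSC rates of the pilot trial used for the sample size, on independence between patients and on full enrolment of 257 per arm. The ROSC-related shift adds a further assumption and ranges from a ratio of 1.31 to 1.09 or less as more non-ROSC patients are evaluated. It is a possible source of distortion, not an established one.

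The documents also leave open whether the count is an absolute cap or is meant to reflect excess over BVM, and automatic termination sits uneasily beside the consultation described in the DSMB section. These passages must be reconciled. The level is for the sponsor and DSMB to set.

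**What to change.** - Record two items for every patient in both arms, from the hospital reports already collected: potential barotrauma (yes/no) and whether the patient was evaluable, taken as chest imaging in the record.
- Give the DSMB cases over evaluable patients, by arm, at each review and whenever the count is reached.
- Have the sponsor and DSMB state whether the count is an absolute cap or is to be judged against the BVM arm, and reconcile the mandatory wording with the DSMB consultation.

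The cost is a protocol amendment and two extraction fields, with no added imaging. The protocol does not say whether the hospital reports show imaging, so this should be confirmed with the receiving hospitals. Evaluability will remain incomplete, but the board will be able to see how incomplete it is in each arm.
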